### **3.4.8 Blinding**

A single blinding will be applied involving the participants. Respondents will not be aware of the intervention allocation, but the researcher and those involved in providing the intervention module will be aware of the allocation. Blinding will be ensured by using an encrypted username for the participants. Participants will also be reminded not to share the content of the intervention.

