#### **3.3 Study Design**

This study is a randomized controlled trial study with two arms involving intervention and a control group. Foundation students at University Putra Malaysia will be recruited to join the study. They will be explained about the study objectives, activities that will be required to do if agree for participating. Participants who consented to join the study will then be randomized to either the intervention or control group. Baseline measurement will be taken prior to

intervention. The intervention group will be given a theory-based health education intervention via a newly developed website, whereas the control group will be waitlisted. The intervention will be conducted for two weeks. Measurement will be repeated after the intervention (2 weeks) and at follow-up (1 month). The flow diagram of the study conduct based on the CONSORT 2010 statement (Schulz et al., 2010) is shown in Figure 3.1.

[figure not shown]

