#### 3.7.1 Questionnaire

The questionnaire will be in dual language (English and *Bahasa Melayu*) where the back-to-back translation will be conducted. All parts of the questionnaire will be self-administrated. The questionnaires consist of the following six sections.

To measure the primary outcome, which is mental health literacy, the questionnaire will be adapted from the Mental Health Literacy Scale (MHLS) (M. O’Connor & Casey, 2015). The internal consistency of MHLS were reported to be  $\alpha=0.8793$ . Whereas, to measure the secondary outcome which is the help-seeking behaviour, the Attitudes Toward Seeking Professional Psychological Help Scale- Short Form (ATSPPH-SF) (Elhai et al., 2008) will be used. The internal consistency of ATSPPH-SF was reported to be  $\alpha=0.77$ . The factor analysis of ASPPH-SF revealed three dimensions includes “openness to seeking professional help”, “value in seeking professional help”, and “preference to cope on one’s own” (Picco et al., 2016).

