### **3.7.2.2 Implementation of Health Intervention Program**

The health education intervention will be implemented after the baseline assessment was conducted. The health education intervention will be given over a period of 2 weeks with 1 month follow-up. The intervention will be done in four sessions, with two sessions weekly. Each session will take approximately 10 minutes to complete.

The participants will be given a link to the website and an id number. The id number will also be their username to access the website of the health education intervention. This is to ensure that non-participants have no access to the education intervention and as monitoring for completion of the intervention. Weekly email and WhatsApp reminders will also be given to participants to prompt them to complete the session.

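### Section 3.4.8 calls the trial single-blind for participants, but a website programme compared with a waitlist, with no sham or attention control, gives no credible participant blinding of self-reported outcomes

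*Combined protocol and SAP*

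**What the plan says.** Section 3.4.8 (Blinding) claims participant blinding: "A single blinding will be applied involving the participants. Respondents will not be aware of the intervention allocation". It names one mechanism: "Blinding will be ensured by using an encrypted username for the participants". It adds a reminder to participants not to pass on the content. The same section says that "the researcher and those involved in providing the intervention module will be aware of the allocation".

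Section 3.3 (Study Design) sets out the contrast: "The intervention group will be given a theory-based health education intervention via a newly developed website, whereas the control group will be waitlisted". Before consent, students hear the aims and what they will have to do: "They will be explained about the study objectives, activities that will be required to do if agree for participating".

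Section 3.7.2.2 describes the exposure: "The intervention will be done in four sessions, with two sessions weekly". Each session lasts about 10 minutes and is reached through a link and an ID that doubles as the username, with weekly email and WhatsApp prompts to complete sessions.

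Section 3.7.1 says of the outcome instrument: "All parts of the questionnaire will be self-administrated". It covers both the primary outcome (mental health literacy) and the secondary outcome (help-seeking).

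**The concern.** The blinding statement and the design do not fit together. A student who logs in and works through four teaching sessions can tell that they are being taught, and a student placed on a waiting list can tell that they are not. Since participants rate themselves, they are also the outcome assessors, so lack of participant blinding acts directly on the measurements.

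The plan therefore claims a protection against response bias that the described design does not provide, and a report repeating the single-blind label would carry the error forward. The exposure is greatest for the attitude and willingness items of the literacy scale and for the help-seeking scale, where knowing that one has been taught the desired answer can move the rating. Factual recognition items are probably less exposed.

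**Working it through.** **Step 1. What each measure in Section 3.4.8 can do.**

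- *Encrypted username.* This hides identity. Section 3.7.2.2 gives two purposes for the login: keeping non-participants out and monitoring completion. Neither masks allocation.
- *Reminder not to share content.* This limits contamination. It also presupposes that recipients know they hold content.
- *Allocation by an outside person (Section 3.4.7).* This is allocation concealment. It protects the assignment step and masks nobody afterwards.

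**Step 2. Is there anything in the control arm that could mask allocation?** The only control condition named is the waitlist (Section 3.3 and the control column of Table 3.3). No sham, placebo or attention-control website is described. The plan's own literature review (Table 2.4) records a web-based trial whose controls received links to pages on unrelated health topics, so the option was known.

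**Step 3. Who could still be blind?**

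| Role | What the document says |
|---|---|
| Participant | Declared blind; the design gives no credible means |
| Researcher and providers | Declared aware of allocation (3.4.8) |
| Outcome assessor | The participant, by self-completed questionnaire (3.7.1) |
| Analyst | Not addressed in 3.4.8 or 3.10 |

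**Step 4. Text that leaves the control condition unclear.** Table 3.3 ticks every component for both arms, under a control column headed as waitlist. Section 3.7.2.2 gives the link, ID and reminders to participants without restricting them to one arm. Section 3.7.2.3 says evaluation of the education process will also be done in the control group. Delayed access is the likely reading, but no section says when it occurs.

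**Step 5. Size (illustration; the shift is assumed).** The plan has no figure to reproduce on this point. Take no true effect, a reporting shift of s standard deviations in the taught arm, n per arm and an unadjusted two-sided 5% test under the normal approximation:

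λ = s × √(n/2); false-positive rate = 1 − Φ(1.96 − λ) + Φ(−1.96 − λ).

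The values of n are 66 per arm (Section 3.4.9) and 33 per arm, which is 66 × (1 − 0.5), the number left if the planned 50% loss occurs.

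| Assumed shift s | λ, n = 33 | False positives, n = 33 | λ, n = 66 | False positives, n = 66 |
|---|---|---|---|---|
| 0.1 SD | 0.41 | about 7% | 0.57 | about 9% |
| 0.2 SD | 0.81 | about 13% | 1.15 | about 21% |
| 0.3 SD | 1.22 | about 23% | 1.72 | about 41% |

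Worked case: s = 0.2, n = 33 gives λ = 0.2 × √16.5 = 0.81, and 0.126 + 0.003 = 0.128. At 44 per arm, the plan's number before inflation for loss, the rates lie between the two columns (about 8%, 16% and 29%).

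**The case against.** The strongest reply is that awareness of allocation is not documented. The consent pages and the flow diagram are not available for review, so what controls are told cannot be checked, and some masking to the hypothesis is conceivable. This stands as a limit on certainty. It does not rescue the label, because the plan describes no such masking and the one mechanism it names cannot provide it.

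A reader might infer that nobody in the trial is blind. The documents do not support that: they do not say who analyses the data or whether that person knows the allocation.

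A reader might also infer that controls certainly receive nothing before the last measurement. That too goes beyond the text, given the unclear passages in Table 3.3 and Sections 3.7.2.2 and 3.7.2.3. Nor would simultaneous access in both arms save the blinding claim, because there would then be no contrast to test.

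The illustration has limits as well. The shift is assumed, and the calculation is for an unadjusted two-group comparison, whereas Section 3.10.2 judges effectiveness on the group-by-time interaction in a GEE model. Converting the shift into points, or into a share of the planned difference, with the figures in Table 3.1 would be wrong: they come from a study that used a different questionnaire.

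Finally, waitlist controls are common in this field, as the plan's review shows, and lack of blinding is then ordinarily a limitation to disclose. That is fair, but this plan states the opposite of the limitation.

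**Conclusion.** The participant-blinding statement is wrong as written. The conclusion rests on the design as described (website programme compared with waitlist, no sham or attention control, self-completed outcomes) and on the inference that participants can tell whether they were given the programme. It does not depend on any assumed bias.

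The size of the bias is unknown from the documents. Across assumed shifts of 0.1 to 0.3 SD, the false-positive rate runs from about 7% to 23% at 33 per arm and from about 9% to 41% at 66 per arm, against a nominal 5%. For a given shift the rate is higher in the larger sample: recruiting more students does not dilute this bias. The sample size, instruments and choice of tests are untouched by this point; what changes is what the trial may claim.

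**What to change.** 1. Replace the blinding statement in Section 3.4.8 with: 'Open-label; participants and intervention providers are not blinded; outcomes are self-reported.' State when the waitlist arm gets access. If the waitlist is meant to serve as control throughout, say that access follows the 1-month measurement; if not, reconcile Section 3.3, Table 3.3 and Sections 3.7.2.2 and 3.7.2.3.
2. Run the analysis on a dataset with arms coded A/B and study IDs replaced by new codes, unmasking only afterwards. New codes are needed because the IDs are also the website usernames used to monitor completion. This guards against analyst bias only; it does nothing about participants' expectations.
3. State in the conclusions that expectation or desirability bias in self-report cannot be excluded, especially for attitude and help-seeking items.

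**Cost:** protocol wording, and a small recoding task for the outside person who already does the randomisation, which Section 3.4.7 does not currently assign. The design will look less favourable. An attention-control website would address participants' expectations more directly, but it would change the control arm and is a larger undertaking than this correction.

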### **3.4.9 Sample Size**

The sample size ( $n_1$ ) for this study was calculated by using the two population mean formula for hypothesis testing (Lemeshow et al., 1990). The sample size calculated was based on the mean Mental Health Literacy Score before and after the intervention. The summary of the sample size calculation is shown in Table 1.

$$N1 = \frac{2SD^2 (z(1-\alpha/2) + z(1-\beta))^2}{(\mu1-\mu2)^2}$$

Where,

N = sample size estimate

S = pooled standard deviation

$Z_{1-\alpha/2}$  = 1.96 (confidence level of 95%,  $\alpha$  is 0.05)

$Z_{1-\beta}$  = 0.84 (power of 80%,  $\beta$  is 0.2)

$\mu1-\mu2$  = estimated mean difference of two groups

$S^2$  = pooled standard deviation. This is calculated according to IUPAC (IUPAC, 2006) criteria given the equation;

$$S_P = \frac{(n_1-1)s_1^2 + (n_2-1)s_2^2 + \dots + (n_k-1)s_k^2}{n_1 + n_2 + n_3 + \dots + n_k - k}$$

Where;

$S_p$  is the Pooled Standard deviation

$n_1$  = number of participants in the control group

$n_2$  = number of participants in the intervention group

$s_1$  = standard deviation of mental health knowledge in the control group

$s_2$  = standard deviation of mental health knowledge in the intervention group

**Table 3.1 Summary of Sample Size Calculation**

| Reference
s                     | Mean (sd)
interventi
on group | N
interventi
on group | Mean
control
group | N control
group | Sp   | n1 |
|------------------------------------|-------------------------------------|-----------------------------|--------------------------|--------------------|------|----|
| Campos
et al.,
2018 | 75.91
(8.13)                     | 239                         | 69.02
(8.23)          | 263                | 8.18 | 44 |

The total sample size in ( $n_1$ ) in this study is 88 (44 participants per arm). After considering 50% loss to follow up, a final sample size of 132 (66 participants per arm) was determined to be sufficient for this study.

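### Table 3.1 gives 44 per arm, but the plan's own formula and inputs give 22.1 (23 per arm), so the 80% power statement does not describe the planned size

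*Combined protocol and SAP*

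**What the plan says.** Section 3.4.9 states that the sample size was "calculated by using the two population mean formula for hypothesis testing" and prints the formula N1 = 2 SD² (z(1−α/2) + z(1−β))² / (μ1−μ2)². The first normal quantile is given as "1.96 (confidence level of 95"%) and the second as "0.84 (power of 80"%). The denominator is the square of the "estimated mean difference of two groups".

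Table 3.1 takes its inputs from one published school-based literacy trial: intervention mean 75.91 (SD 8.13, N 239), control mean 69.02 (SD 8.23, N 263), pooled SD 8.18. Its last column prints n1 = 44.

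The text below the table says that the total "in this study is 88 (44 participants per arm"). It continues: "After considering 50% loss to follow up", with "a final sample size of 132 (66 participants per arm") as the result.

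**The concern.** The leading factor 2 in the formula is the sum of two equal group variances, so the formula returns the number in one arm. The plan reads n1 that way too, since it doubles 44 to get 88. But 44 is not what the formula returns with the tabulated inputs.

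This is the only sample-size justification in the plan. The 88, the 66 per arm and the 132 are all built on 44. If 44 is wrong, the stated 80% power does not belong to the stated number, and anyone who repeats the one-line calculation will find that the justification fails.

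**Working it through.** **Inputs** (Section 3.4.9 and Table 3.1): z = 1.96 and 0.84; SDs 8.13 (N 239) and 8.23 (N 263); means 75.91 and 69.02; pooled SD 8.18; equal arms.

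**1. Pooled SD.** (238 × 8.13² + 262 × 8.23²) / 500 = 66.95, and √66.95 = 8.18. This matches the table, so the inputs are intact.

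**2. Difference.** 75.91 − 69.02 = 6.89. The standardised difference is 6.89 / 8.18 = 0.842.

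**3. The plan's formula.** 2 × 8.18² × (1.96 + 0.84)² / 6.89² = 2 × 66.91 × 7.84 / 47.47 = 1049.2 / 47.47 = **22.1 per arm**, rounded up to 23, or 46 in total. The table's 44 is not reproduced.

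**4. Can another reading give 44 per arm?** With the same difference and SD:

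| Setting | n per arm |
|---|---|
| One-sided 5%, 80% power | 18 |
| Two-sided 5%, 90% power | 30 |
| Two-sided 5%, 95% power | 37 |
| Two-sided 5%, 97.5% power | 44 |
| Two-sided 1%, 80% power | 33 |
| Two-sided 1%, 90% power | 42 |
| Two-sided 1%, 95% power | 51 |
| Two-sided 5%, 80% power, 8.18 entered as a variance | 2.7 |

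Only about 97.5% power gives 44, and the plan states 80%. Using 5.693, the literacy effect that Table 2.5 lists for the same source study, as the difference gives 33 per arm. At the stated error rate and power, the one figure that matches is the unrounded total for both arms, 2 × 22.1 = 44.2.

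**5. Power on the plan's inputs** (two-sided 5%, standardised difference 0.842):

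| Evaluable per arm | t-test | Normal approximation |
|---|---|---|
| 22 | 77.9% | 79.8% |
| 23 | 79.8% | 81.5% |
| 33 | 92.1% | 92.8% |
| 44 | 97.4% | 97.7% |
| 66 | 99.8% | 99.8% |

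**6. Attrition step.** The plan multiplies by 1.5: 44 × 1.5 = 66 per arm. If half of 66 are lost, 33 per arm remain. That is below the printed 44 but above the corrected 23.

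**The case against.** The strongest counter-argument is about weight. The error is in the safe direction. On the plan's inputs the trial keeps 92% power even if half of the 66 per arm are lost, and type I error, bias and the primary comparison are unaffected. On this view the defect is one of documentation. The direction is rightly described, and it is why enrolment need not change. It does not make the printed figure correct.

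Other points against:

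- The chain 44 → 88 → 132 is consistent with itself (44 × 1.5 = 66). That is true; only the step from the formula to 44 fails. Whether multiplying by 1.5 is the right allowance for 50% loss is a separate matter.
- The cause is not documented. That a two-arm total was doubled is an inference, and reaching 44 that way needs 44.2 rounded down. The mismatch does not depend on the explanation.
- The planned between-group comparison in Section 3.10.2 is a t-test. There, 23 per arm gives 79.8%, and 24 per arm are needed to pass 80%. This stands: 23 is the output of the plan's normal-quantile formula, and the t-test figure is one higher.
- The inputs come from a study that Table 2.5 lists as using its own questionnaire (MHLq), while this trial uses the Mental Health Literacy Scale (MHLS). The documents give neither an SD nor an expected difference for the MHLS. This also stands. As an illustration only, if the SD were 11.5 with the same difference of 6.89, the formula would give 2 × 11.5² × 7.84 / 47.47 = 43.7, so 44 per arm would have about 80% power. The plan does not make that argument, but it is a reason not to cut enrolment on the strength of the corrected figure.

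**Conclusion.** The point holds. With the plan's formula and tabulated inputs, n1 is 22.1, or 23 per arm (46 in total), against a printed 44 per arm (88 in total): a factor of 2. Nothing else in the document accounts for 44.

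On those inputs, 44 evaluable per arm has 97.4% power by t-test, not 80%. The final 132 is not undermined: after a 50% loss it leaves 33 per arm and about 92% power. All these power figures assume a difference of 6.89 and an SD of 8.18, both measured on a different scale from this trial's primary outcome, so the true power on the MHLS cannot be derived from the documents.

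**What to change.** In Table 3.1, replace n1 = 44 with 23 per arm, and in the text below it replace 88 with 46 in total. If the t-test is the intended basis, use 24 per arm (48 in total) and say so.

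If 44 per arm or 132 in total is kept as a deliberate margin, state that and give the power: 97% at 44 evaluable per arm, and 92% at the 33 per arm left if half of the 66 enrolled are lost, each for a difference of 6.89 and SD of 8.18. Add one sentence saying that these inputs were measured with the MHLq and not the MHLS, so the power is conditional on their carrying over.

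The cost is a rewording of Section 3.4.9 and Table 3.1. No change in enrolment, design or analysis is needed.

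### Section 3.4.9 allows for 50% loss by multiplying by 1.5 instead of dividing by 0.5, so its sample-size sentence is wrong as written, although 132 is still enough at the planned effect

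*Combined protocol and SAP*

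**What the plan says.** Section 3.4.9 uses the standard formula for comparing two means. Its z values are "1.96 (confidence level of 95"% and "0.84 (power of 80"%, and the denominator is the square of the "estimated mean difference of two groups". Table 3.1 takes the inputs from one school-based trial: mean 75.91 (SD 8.13, n = 239) with intervention, mean 69.02 (SD 8.23, n = 263) in control, a pooled SD of 8.18, and n1 = 44.

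The text under the table says that the total "in this study is 88 (44 participants per arm"). It then allows for attrition: "After considering 50% loss to follow up, a final sample size of 132 (66 participants per arm) was determined to be sufficient". The section gives no other loss rate and no other reason for the increase from 88 to 132.

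**The concern.** A loss rate applies to the people enrolled. To keep n participants after a fraction d is lost, enrolment must be n/(1 - d). Multiplying by (1 + d) instead gives too few, and the gap widens as d grows. At 50% it is large: the factor should be 2 and the plan uses 1.5.

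An ethics committee or a later reader relies on this sentence to judge how much attrition the trial can absorb. As written, it says that the stated need of 44 per arm survives a loss that would in fact leave fewer.

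**Working it through.** **Inputs.** From Section 3.4.9 and Table 3.1: two-sided alpha 0.05 (z = 1.96), power 80% (z = 0.84), difference 75.91 - 69.02 = 6.89, pooled SD 8.18, stated need 44 per arm (88), loss 50%, final size 66 per arm (132).

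**1. Reproduce the stated final size.** 44 × 1.5 = 66 and 88 × 1.5 = 132, so the plan's rule is n × (1 + d).

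**2. Apply the stated loss.**
- Remaining per arm: 66 × (1 - 0.5) = 33. That is 11 fewer than 44, or 25% short (11/44).
- Loss at which 66 still leaves 44: 1 - 44/66 = 33.3%.
- Enrolment that leaves 44 after 50% loss: 44/(1 - 0.5) = 88 per arm, 176 in total.

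**3. Check the 44 itself.**
- Pooled SD: √[(238 × 8.13² + 262 × 8.23²)/500] = 8.18, which agrees with Table 3.1.
- Formula: 2 × 8.18² × (1.96 + 0.84)² / 6.89² = 2 × 66.91 × 7.84 / 47.47 = 22.1, so 23 per arm.
- The stated 44 is not reproduced as a per-arm figure at 80% power. It is close to 2 × 22.1 = 44.2, which suggests that a two-arm total was read as a per-arm number and then doubled to 88. That explanation is an inference; the documents do not give it.

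**4. Inflate correctly from the plan's inputs.**
- Normal approximation: 23/(1 - 0.5) = 46 per arm, 92 in total.
- t-test: 23 per arm gives 79.8% power and 24 gives 81.5%, so 24 are needed. 24/0.5 = 48 per arm, 96 in total.
- Both totals are below 132.

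**5. Power for a difference of 6.89 (SD 8.18, two-sided 0.05).**

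| Completers per arm | Normal approximation | t-test |
|---|---|---|
| 23 | 81.5% | 79.8% |
| 33 | 92.8% | 92.1% |
| 44 | 97.7% | 97.4% |

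**6. Sensitivity range, under an assumption.** Table 2.5 lists 5.693 (4.682, 6.704) for the same source trial and does not label it. Assume that it is a between-group mean difference with its interval, on the same scale, and that the SD of 8.18 applies. Then t-test power at 33 per arm is 79.5% for 5.693 and 62.9% for 4.682.

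**The case against.** The strongest defence is that the conclusion survives. The sentence says 132 is sufficient with 50% loss. On the section's own formula and inputs this is true, because 92 or 96 would do. The shortfall of 11 per arm is measured only against 44, which those inputs do not support. This stands. It limits the point to a wrong derivation and a wrong statement about attrition.

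It can also be said that 33 is a worst case. Section 3.5.1 plans two post-baseline measurements, and Sections 3.10.1 and 3.10.2 name intention to treat and GEE. Someone lost by 1 month may still contribute a 2-week score. This stands too, as a caveat on the count of 33. It does not make half of 66 equal 44.

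A third reply is that 50% was meant as a mark-up on the sample size. The sentence calls it loss to follow-up. If a mark-up was meant, the loss it covers is 33.3%, and the text should say so.

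Three stronger readings are tempting, and the documents support none of them:
- A reader might infer that the trial is underpowered. At 33 per arm the power for the planned difference is about 92%, against a target of 80%.
- A reader might infer that enrolment should rise to 176. That follows only if 44 per arm is the true requirement for 80% power, which would imply a difference of about 4.88 (8.18 × √(2/44) × 2.8), with about 68% power at 33 per arm. The plan states no such difference.
- A reader might take the 79.5% and 62.9% in the sensitivity range as the trial's real power. They rest on an unlabelled table entry combined with an SD from another table. Whether 6.89 is optimistic is a separate question from the attrition arithmetic.

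**Conclusion.** The inflation step in Section 3.4.9 is wrong. At the plan's own 50% loss, 66 enrolled per arm leaves 33, a quarter below the 44 it says it needs. The stated 44 is protected only up to 33.3% loss.

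The practical effect is small because 44 is itself about twice what the formula gives, so the two errors offset each other. Correcting only the inflation would call for 176 participants that the inputs do not justify. Correcting only n1 would leave a wrong inflation rule in the protocol.

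This is a correction to a stated figure, with no change to enrolment. It assumes that those lost give no post-baseline data and that the difference of 6.89 and SD of 8.18 carry over to this trial. The second assumption is the plan's own. Table 2.5 shows that the source trial used its own questionnaire (MHLq), whereas Section 3.7.1 adapts the MHLS.

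**What to change.** Keep 132 and make these changes to Section 3.4.9 and Table 3.1 in one edit:
- Correct n1 to the value that the formula gives: 23 per arm (22.1 rounded up), or 24 if the t-test is used. Do not keep 44 per arm as the requirement for 80% power.
- State the inflation rule as n/(1 - loss). With 50% loss this gives 46 per arm (92 in total), or 48 per arm (96 in total) by the t-test.
- Replace the final sentence with wording such as: *With 50% loss to follow-up, 132 enrolled leaves 33 per arm, giving about 92% power for a difference of 6.89 (SD 8.18, two-sided 0.05).* Add that this assumes no post-baseline data from those lost.
- If smaller effects are shown, give about 80% power for 5.69 and about 63% for 4.68 as a sensitivity range only, and state the assumption about the Table 2.5 entry beside them.

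The cost is a few sentences and one table cell. No participants are added and the planned analysis does not change.
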